### Data management

The two surveys used online Qualtrics tool (https://www.qualtrics.com). InterRAI assessments are also conducted online, using the same systems as all NZ needs assessments are undertaken. Electronic lists of the unique study identification numbers, date of consent to the study and NHI number will be sent to the interRAI organization and MoH for data extract purposes. Outcome and health service use data will then be provided by interRAI and the MoH by secure link to the researchers, identified by study ID, i.e. without NHI numbers, names or any other identifiers. Data are stored on password-protected shared drives available only to bona fide members of the university research team, and located in locked University offices.

Similarly, health outcomes data for the Survey phase and the RCT will be obtained from MoH from an electronic file supplied by the research team, following an approval process. Data from the two surveys, from interRAI and from MoH will be imported into SAS version 9.4 (SAS Institute Inc., Cary. NC, USA) used for all analyses.

### Power and sample size calculation

Initial power calculation for the RCT was performed prior to commencement of the Survey phase. Following commencement of the Survey phase it became apparent that the subjects were of higher medical acuity and vulnerability than we had anticipated and revised power calculations for the RCT were performed before RCT commencement.

Sample size for the Survey phase follow-up phases was largely governed by the sample needed for the RCT. An estimated 65% of the Survey phase follow-up residents were eligible for the RCT, meaning that 572 residents were needed in the Survey phase. An average of 2.5 years follow-up will be available for the Cohort phase by January 2020. If the rate of acute hospitalisation (primary outcome) is 55% per year we will have at least 80% power to show a 20% difference in the hazard ratio for any two categories.

For the RCT, we estimated 372 residents met the “high-risk” criteria, will be randomised and followed for 1 year after randomisation. The rate of acute hospitalisation in LTC residents is 67% per year (from previous work). We conservatively hypothesised the acute hospitalisation rate in the “high risk” RCT RV residents would be 70% per person-year. We would expect 80% power to show a 20% reduction in our primary outcome (acute hospitalisation). If the effect is stronger (e.g. 25% or 30% - as found in our ARCHUS [16] and ARCHIP [18] studies or longer follow-up, power will increase, though based on our earlier work (ARCHIP), the duration of any intervention effect may be under 1.4 years.

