##### Cohort study follow-up

Study outcomes will be to describe trajectories of healthcare utilisation. The primary outcome will be first acute hospitalisation, while secondary outcomes will number of all acute hospitalisations, LTC admissions and all-cause mortality. All are available from routinely collected Ministry of Health (MOH) administrative data, by use of each individual’s unique National Health Identifier (NHI). For any subjects declining entry into the RCT (below), GNSs confirmed their continued permission to obtain these centrally-held data.

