### Statistical analysis

In the Survey phase, initial descriptive analyses will be conducted. Then, in both the Survey and Cohort phases, multivariate regression models (including logistic regression, log-binomial regression, linear regression and Cox regression) will be used to explore the influence factors on health outcomes adjusting for potential confounders (demographics, lifestyle, medical history, clinical characteristics, village characteristics etc.) and time to event when possible.

For the primary and main secondary outcomes in the RCT, analyses will be conducted on an intention-to-treat basis. Cox proportional regression models, with robust sandwich variance estimates, will be used to compare the time to health outcomes between the intervention and usual care groups. Hazard ratios (HRs) and 95% confidence intervals (CIs) will be calculated. Sub-group analyses will evaluate treatment effect for the main endpoint for different sub-groups, e.g. subgroup analyses for each endpoint by sex, large/small village, clinic/nurse/not, sampled/volunteers. Analyses will be conducted by a research statistician not involved in the clinical aspects of the study.

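### The Cohort-phase claim of at least 80% power for a 20% hazard difference between any two categories is not supported by its own inputs; under two-sided 5% the power is 64–70% at best

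*Protocol article*

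**What the plan says.** The claim is in the protocol article under Power and sample size calculation. The cohort size is derived from the needs of the randomised trial: an estimated 65% of surveyed residents would be eligible, "meaning that 572 residents were needed in the Survey phase". Follow-up is given as "An average of 2.5 years follow-up will be available for the Cohort phase by January 2020". The power statement is conditional: "If the rate of acute hospitalisation (primary outcome) is 55% per year", then "we will have at least 80% power to show a 20% difference in the hazard ratio for any two categories".

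The section Cohort study follow-up fixes the endpoint: "The primary outcome will be first acute hospitalisation, while secondary outcomes will number of all acute hospitalisations". The Cohort follow-up rows of Table 1 agree. Each resident can therefore contribute at most one primary event.

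Under Statistical analysis, for the Survey and Cohort phases, "multivariate regression models (including logistic regression, log-binomial regression, linear regression and Cox regression) will be used", with adjustment for potential confounders. No alpha, sidedness or category split is given for the Cohort power statement. The nearest indication of a significance level is in the trial's analysis text: "Hazard ratios (HRs) and 95% confidence intervals (CIs) will be calculated".

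**The concern.** For a time-to-event comparison, power depends on the number of events and on how they divide between the categories. The article supplies what is needed to work out the expected number of first events, and that number looks too small for a hazard ratio of 0.80. The phrase about any two categories widens the claim to unequal splits and to pairs of levels within a multi-level factor, both of which carry less information than an equal split of everyone.

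Describing residents' healthcare trajectories is a stated objective, and the Cohort models are meant to explore what influences health outcomes. If the stated power is taken at face value, a null association for a modest risk factor could be read as better evidence of no association than the data can give.

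**Working it through.** **Inputs from the article.** N = 572; rate 55% per year; average follow-up 2.5 years; endpoint first acute hospitalisation; target power at least 80%; a 20% difference on the hazard-ratio scale. The cohort size reproduces: 372/0.65 = 572.3.

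**Assumptions.** Two-sided 5%, in line with the 95% confidence intervals used elsewhere, with one-sided 5% as a variant. The 20% difference is read as HR 0.80 (or 1.25, its equivalent on the log scale), which is more favourable than HR 1.20. The split p is not stated, so 50:50 (the best case), 30:70 and 20:80 are shown. All residents are followed for exactly 2.5 years, which also favours the claim, because spread around the same mean lowers the expected number of first events.

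**Events required** (Schoenfeld): d = (z_alpha + z_power)² / [p(1−p)(ln HR)²].

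- Two-sided 5%, HR 0.80, 50:50: 7.849 / (0.25 × 0.2231²) = 630.5, so 631. Freedman's formula gives 636.
- Two-sided 5%, HR 1.20, 50:50: 944.5, so 945.
- Two-sided 5%, HR 0.80, 20:80: 985.
- One-sided 5%, HR 0.80, 50:50: 497.

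**First events expected.**

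- 55% as a hazard: 572 × (1 − exp(−0.55 × 2.5)) = 427.
- 55% as an annual risk: 572 × (1 − 0.45^2.5) = 494.
- Ceiling, every resident hospitalised: 572.

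**Power for HR 0.80 or 1.25:** Φ(√(d·p(1−p)) × 0.2231 − z_alpha). For example, with 427 events at 50:50, √(427 × 0.25) × 0.2231 − 1.96 = 0.35, giving 64%.

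| First events | Alpha | 50:50 | 30:70 | 20:80 |
|---|---|---|---|---|
| 427 | two-sided 5% | 63.6% | 56.1% | 45.4% |
| 494 | two-sided 5% | 69.9% | 62.3% | 51.0% |
| 572 (ceiling) | two-sided 5% | 76.1% | 68.6% | 56.9% |
| 427 | one-sided 5% | 74.6% | 68.1% | 57.9% |
| 494 | one-sided 5% | 79.8% | 73.5% | 63.3% |
| 572 (ceiling) | one-sided 5% | 84.7% | 78.8% | 68.8% |

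For HR 1.20 at two-sided 5% and 50:50, power is 47–53%. A log-rank simulation (5,000 runs, equal groups, HR 0.80, 55% applied to the reference group, two-sided 5%) gave 61% with 55% as a hazard, 70% with 55% as an annual risk, and 76% with an event in every resident.

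**HR detectable with 80% power**, two-sided 5%: exp(2.80/√(d·p(1−p))). At 50:50 this is 1.31 (427 events) to 1.29 (494), or 0.76 to 0.78 in the other direction. At 20:80 it is 1.40 to 1.37.

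**Could another calculation have produced the stated figure?**

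- All hospitalisations: 572 × 2.5 × 0.55 = 786 events, giving 87.9% at 50:50 but 70.7% at 20:80.
- A two-proportion test of a 20% relative reduction in 2.5-year risk: 97% or more at 50:50.
- For comparison, the randomised trial's own 80% reproduces as a two-proportion test (70% against 56%, 186 per arm: 80.1%).

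**The case against.** A reader might infer that the claim is impossible, since 631 required events exceed 572 residents. The documents do not support that. The 631 rests on a two-sided 5% alpha that the article does not state for this calculation. At one-sided 5%, 497 events suffice at 50:50, and 572 events would give 84.7%, so the ceiling alone does not settle the matter. Also, 572 is the number said to be needed; the number enrolled is not reported, and the ceiling applies only to the plan as written.

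These points temper the wording without rescuing the claim. At one-sided 5% the expected events give about 75–80% with a perfectly equal split and 58–63% at 20:80. Even with every resident hospitalised, a 30:70 split gives 78.8%.

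The figure might instead come from counting all hospitalisations or from comparing proportions. The first conflicts with the power sentence, which names the primary outcome, and with the Cohort section, which makes the count of all hospitalisations secondary. The second is not a hazard ratio. The article says neither.

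It is fair to add that the Cohort phase is exploratory and was sized by the trial, so no confirmatory test depends on this sentence. A reader might also want to add village clustering to the charge. Table 1 discusses clustering only for the trial's power calculation, and nothing in the article allows its size to be worked out for the Cohort phase, so it forms no part of this point.

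**Conclusion.** The stated Cohort power is wrong as written. With 572 residents, 2.5 years, 55% per year and first acute hospitalisation as the endpoint, power for HR 0.80 or 1.25 is 64–70% in the most favourable split and 45–51% at 20:80, against a stated minimum of 80%. This assumes two-sided 5%, no confounder adjustment, and two categories that together cover the whole cohort. Sidedness changes the size of the shortfall, but neither choice supports at least 80% for any two categories.

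The sentence should be corrected, but the error is limited in reach: it concerns an exploratory observational phase and leaves the trial's sample size, primary outcome and analysis untouched.

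**What to change.** Replace the power sentence with one that states its assumptions, for example:

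> With 572 residents and an expected 427–494 first acute hospitalisations (55% per year read as a hazard or as an annual risk), at two-sided 5% and before confounder adjustment, the Cohort phase has 80% power for a hazard ratio of about 1.3 (or 0.77) between two equal-sized categories covering the whole cohort, and about 1.4 for a 20:80 split; power for a hazard ratio of 0.80 or 1.25 is 64–70% at best.

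If the authors' figure came from a test of proportions, say so and drop the reference to a hazard ratio. If it counted all hospitalisations, say so and drop the label of primary outcome.

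The change is to one sentence, with no further enrolment and no change to design or data collection. The only cost is a less favourable stated figure.

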Internationally, RVs have been shown to impact positively on residents’ wellbeing, with higher quality of life compared to those living in family homes or in LTC [9, 10]. NZ research has shown that RV residents are more educated, have more financial resources and better well-being, but have significantly greater functional dependency compared with those in private dwellings [11]. It is clear that only those with substantial financial resources can afford the significant personal investment required initially (NZ$250,000– NZ$1 M+) and the (usually) on-going monthly service fees, [8] resulting in inequity in access.

An increase in the ageing population in NZ is projected over the next decade. The number of older people living within RVs will also likely increase, who as they age will be more prone to increased frailty, greater health needs and declining independence. Indeed, it is likely that RV residents may include a proportion of frailer dependent older people that would have previously resided in LTC facilities [4, 5]. However, little is known in NZ, or elsewhere, about health or functional needs of this potentially vulnerable group of older people, or of what services are or are not provided by RVs to their residents.

In 2012 we completed a small feasibility survey of the functional status, dependency & social circumstances of 110 participants in Auckland RVs [12]. Forty-five percent had been assessed for publicly funded homecare help while 15% received help with personal cares. They had higher morbidity and need (vs. community-dwelling older people), including falls, general health, help with bathing/ dressing, and cognition. These findings suggest that physical function of RV residents lies between those living in private homes and those in LTC.

The basis for the current study was our belief that RV residents may have multiple unmet needs together with declining medical and functional ‘trajectories’ with time, and that a targeted intervention might decrease the risk first acute hospitalisation, number of all acute hospitalisations, LTC admissions and all-cause mortality.

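### The RCT's stated 80% power holds only if 70% is a one-year risk and the 20% a risk ratio; with the rate as printed, or a hazard ratio of 0.80, one-year power is about 31–50%

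*Protocol article*

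**What the plan says.** All the RCT power inputs are in the section *Power and sample size calculation* of the protocol article.

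- Size: "For the RCT, we estimated 372 residents met the" high-risk criteria.
- Follow-up: these residents "will be randomised and followed for 1 year after randomisation".
- Control value: the hypothesis, described as conservative, is that hospitalisation in the high-risk "RCT RV residents would be 70% per person-year". Just before it stands a reference figure: "The rate of acute hospitalisation in LTC residents is 67% per year".
- Claim: "We would expect 80% power to show a 20% reduction in our primary outcome (acute hospitalisation").

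The RCT sentences do not name the scale of the 20%, the test, alpha or the allocation ratio. The cohort statement in the same section does name a scale: "at least 80% power to show a 20% difference in the hazard ratio for any two categories".

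The *RCT* section makes first acute hospitalisation the primary outcome, so each resident contributes at most one event. *Statistical analysis* plans Cox models for the RCT: "Hazard ratios (HRs) and 95% confidence intervals (CIs) will be calculated". *Study status* expects a median of 18 months of RCT follow-up by the end of January 2020.

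**The concern.** The power sentence combines a value with a person-year unit, a first-event outcome, a hazard-ratio analysis and a 20% reduction on no stated scale. These choices are not interchangeable when events are common. At a control risk near 70%, a 20% cut in risk is a much larger effect than a 20% cut in hazard, and a rate of 0.70 per person-year is not a 70% risk.

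The trial will report a hazard ratio. A reader who takes the 20% as a hazard reduction, the scale used in the cohort statement, would believe that the trial had an 80% chance of detecting a hazard ratio of 0.80. A non-significant result could then be taken as evidence against a 20% hazard reduction, which the trial is not large enough to provide.

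**Working it through.** **Inputs.** From the article: N = 372, 1 year, 70% per person-year, 20% reduction, 80% power, first event only, Cox hazard ratio. Assumed here because not stated: two-sided 5% (consistent with the 95% intervals), 1:1 allocation (186 per arm), exponential event times, no dropout and no competing deaths.

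**Step 1. Reproduce 372.** Pooled two-proportion formula with risks 0.70 and 0.80 × 0.70 = 0.56, mean 0.63:

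n per arm = [1.96·√(2 × 0.63 × 0.37) + 0.8416·√(0.70 × 0.30 + 0.56 × 0.44)]² / 0.14² = (1.338 + 0.569)² / 0.0196 = 185.5, so 186 per arm and 372 in total.

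Power with 186 per arm is 80.1%. The match is exact, but the test behind it is inferred; the arcsine formula also gives 372.

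**Step 2. Put that alternative on the Cox scale.** HR = ln(0.44)/ln(0.30) = 0.68. Expected events = 186 × (0.70 + 0.56) = 234. Power = Φ(½·√d·|ln HR| − 1.96) = 83.4%; a simulated log-rank test gave 83.3%.

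**Step 3. Take the unit as printed.** A hazard of 0.70 per person-year gives a one-year first-event risk of 1 − exp(−0.70) = 50.3%.

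- 20% as a hazard reduction: the intervention risk is 1 − exp(−0.56) = 42.9%, events = 186 × (0.503 + 0.429) = 173, and power is 31.2% (simulation 31.1%).
- 20% as a risk reduction, 50.3% to 40.3%: two-proportion power is 50%. By Cox, HR = ln(0.597)/ln(0.497) = 0.74 with 169 events, and power is 51%.

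**Step 4. Take 70% as a one-year risk, with HR 0.80.** The intervention risk is 1 − 0.30^0.8 = 61.8%, events = 186 × (0.70 + 0.618) = 245, and power is 41.6% (simulation 41.4%).

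**Step 5. The ceiling at HR 0.80.** Events needed = 4 × (1.96 + 0.8416)² / (ln 0.80)² = 630.5, so 631. At most 372 first events are possible, and with all 372 the power is 57.6%.

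| Meaning of 70% | Meaning of 20% | Power at 1 year | Power at 18 months |
|---|---|---|---|
| One-year risk | Risk ratio 0.80 (HR 0.68) | 80% (two-proportion), 83% (Cox) | not computed |
| Person-year rate | Risk ratio 0.80 (HR 0.74) | 50% (two-proportion), 51% (Cox) | not computed |
| One-year risk | HR 0.80 | 42% | 49% (298 events) |
| Person-year rate | HR 0.80 | 31% | 39% (227 events) |

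**Step 6. The control value.** On the two-proportion basis that yields 372, a control risk of 67% (67% vs 53.6%) gives 75% power in place of 80%. A higher control value therefore raises the stated power.

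**The case against.** The strongest defence is that the RCT sentence never calls the 20% a hazard ratio; that scale is named only for the cohort. If 70% is a one-year risk and the 20% a relative risk reduction, the stated figure is reproduced. The exact match at 372 suggests that this is how it was obtained, with the person-year unit being loose wording. This stands. A reader might infer that the trial simply lacks 80% power for a 20% reduction, or that moving from a two-proportion calculation to Cox loses power. The documents support neither: under 70% vs 56% Cox has about 83%. But the defence needs both readings together, and the text states neither. One of them goes against the printed unit.

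Two other inferences are also too strong.

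- *Effects of 25% or 30%.* The article says only that power will increase, which is true on every scale. On the risk scale it is about 94% and 99%. Only on the hazard scale at 1 year does it stay below 80%: 47–61% at HR 0.75 and 63–78% at HR 0.70.
- *Village residents as less dependent than LTC residents.* The *Background* says "physical function of RV residents lies between those living in private homes and those in LTC". That comes from a survey of 110 participants and concerns physical function. It does not show that 70% is too high for hospitalisation in a group selected as high risk, particularly as the article reports higher acuity than anticipated.

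A condensed article may also leave the test, alpha and allocation to the full protocol, so their absence is not part of this point.

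**Conclusion.** The point holds in a conditional form. The 80% is right for one-year risks of 70% vs 56%, a hazard ratio of about 0.68. It is wrong for the rate as printed: about 31% for a 20% hazard reduction and about 50% for a 20% risk reduction. It is also wrong for a hazard ratio of 0.80 when 70% is a one-year risk: about 42% at 1 year. Across both readings of the 70%, power for a hazard ratio of 0.80 is 31–42% at 1 year and 39–49% at 18 months. No length of follow-up takes it above 58%.

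The word *conservatively* is unsupported as it stands, because 70% exceeds the only reference value given (67%) and a higher value favours power. That is not a contradiction, since the RCT group is selected for risk, but the choice needs a reason.

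The figures rest on the assumptions listed with the inputs. Dropout or competing deaths would reduce the event counts further.

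**What to change.** Reword the RCT power paragraph to:

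- say whether 70% is a one-year risk or a rate per person-year, and on which scale the 20% lies;
- state that 372 residents give 80% power for one-year risks of 70% vs 56%, a hazard ratio of about 0.68, if that was the calculation;
- state that power for a hazard ratio of 0.80 is about 31–42% at 1 year, and that a non-significant result does not exclude a 20% hazard reduction;
- drop *conservatively*, or justify 70% against the 67% quoted for LTC residents and show the effect of the lower value (about 75% power on the two-proportion basis).

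The cost is a few sentences and a less favourable power statement. Randomisation is complete, and the change needs no extra participants and no change to the Cox analysis.

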### Statistical analysis

In the Survey phase, initial descriptive analyses will be conducted. Then, in both the Survey and Cohort phases, multivariate regression models (including logistic regression, log-binomial regression, linear regression and Cox regression) will be used to explore the influence factors on health outcomes adjusting for potential confounders (demographics, lifestyle, medical history, clinical characteristics, village characteristics etc.) and time to event when possible.

For the primary and main secondary outcomes in the RCT, analyses will be conducted on an intention-to-treat basis. Cox proportional regression models, with robust sandwich variance estimates, will be used to compare the time to health outcomes between the intervention and usual care groups. Hazard ratios (HRs) and 95% confidence intervals (CIs) will be calculated. Sub-group analyses will evaluate treatment effect for the main endpoint for different sub-groups, e.g. subgroup analyses for each endpoint by sex, large/small village, clinic/nurse/not, sampled/volunteers. Analyses will be conducted by a research statistician not involved in the clinical aspects of the study.

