Endpoints of interest	Primary endpoint: First cute hospitalisation Secondary endpoints; All acute hospitalisations, LTC admissions, mortality	Primary endpoint: First acute hospitalisation Secondary endpoints: number of all acute hospitalisation, LTC admissions, mortality Power analyses are based on the primary outcome. We did consider changing the primary outcome to ED presentations, but decided against this as, in NZ, many people who are acutely hospitalised are not admitted via ED but go via GP referral to acute admitting units.
Power calculations	That residents were clustered into villages led to power calculations including an adjustment for a cluster effect.	Clustering was catered for by stratified random sampling, and adjustment for cluster effect was unnecessary.

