##### RCT

Based on a combination of the interRAI assessment and selection criteria validated from our ARCHUS study [15] a sub-sample of resident from the baseline phase (initially estimated at about 28%) ‘at high risk’ of health and functional decline, will be selected for inclusion in the RCT (Table 1). These potentially ‘at risk’ residents, eligible for the RCT, will be identified by triggering three or more interRAI CAPS. There will be no additional exclusion criteria applied. After GNSs obtained written, informed consent, eligible residents will then be randomly allocated to the control or intervention arm, stratified by village. The randomisation list will be generated (using computer-based random number generation) by a statistician not involved in outcome measures. This will ensure that the two groups are balanced regarding each RV. The controls will receive no additional contact, assessments or services. The intervention group will receive a GNS-facilitated intervention plan, similar to our ARCHUS study [15]. In brief, this comprises a comprehensive geriatric assessment by a clinical team consisting of a GNS, a geriatrician and a clinical pharmacist reviewing baseline 1 assessments, residents’ medical records and a further update of health issues prior to the MDT meeting. If an urgent significant health issue is identified, intervention subjects will receive a direct referral from the research team to other relevant services and/or a phone call to the GP. Randomisation and MDTs began in March 2017.

The MDT review will occur in collaboration with the older person & their chosen support person(s), geriatrician or nurse practitioner, and clinical pharmacist. This will culminate in an MDT meeting (usually in the resident’s apartment) lasting approximately 45 min, to which the subjects’ general practitioners (GPs) will be invited. Treatment goals and recommendations will be discussed and developed with the resident and all present, and a summary of the MDT meeting with suggestions and recommendations sent by mail to each participant and their GP.

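### RCT allocation is stratified by village but the stated Cox model names no village stratum (a mildly conservative omission), and the Survey/Cohort models state no clustered variance, which would make standard errors for village-level factors too small

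*Protocol article*

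**What the plan says.** **RCT allocation** (Protocol article, RCT section). Residents are individually "randomly allocated to the control or intervention arm, stratified by village". The stated purpose is balance within each village: "This will ensure that the two groups are balanced regarding each RV".

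**RCT analysis** (Statistical analysis). "Cox proportional regression models, with robust sandwich variance estimates, will be used to compare the time to health outcomes" between the two groups. No village stratum, village covariate or village random effect is named, and the unit over which the sandwich is summed is not given. In the RCT paragraph, village appears only through subgroups such as village size.

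**RCT power** (Table 1, RCT block, Power calculations row). Planned: "That residents were clustered into villages led to power calculations including an adjustment for a cluster effect". Implemented: "Clustering was catered for by stratified random sampling, and adjustment for cluster effect was unnecessary".

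**Survey and Cohort analysis** (Statistical analysis). "multivariate regression models (including logistic regression, log-binomial regression, linear regression and Cox regression) will be used" to explore influences on health outcomes, "adjusting for potential confounders (demographics, lifestyle, medical history, clinical characteristics, village characteristics etc". No method for within-village correlation is named. Under Recruitment procedures, residents of larger villages are sampled with a target of about 30 per village. Table 1 adds that eligible co-residents of a unit are both invited.

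**The concern.** Two parts of the plan treat village differently from how the data arise.

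- **RCT.** Stratified allocation makes the arms more alike than simple randomisation would. An analysis without the stratum does not credit that balance. The reported standard error can then exceed the true one, and pooling villages with different baseline hazards moves the hazard ratio slightly towards 1. Some precision is lost.
- **Survey/Cohort.** Residents of one village share its setting and services. A factor that takes one value per village is informed mainly by the number of villages, not the number of residents. Village characteristics as fixed covariates do not remove the remaining within-village correlation. Intervals computed as if residents were independent would be too narrow for such factors, and associations could be reported that are not there. The Discussion intends these results to inform policy and service provision.

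**Working it through.** **1. The plan's own figure.** From Power and sample size calculation: 372 residents, a 70% control rate and a 20% reduction, so 0.70 × 0.80 = 0.56. Assuming 1:1 allocation (186 per arm), two-sided 0.05 and no design effect, a two-proportion comparison gives 80.1% power. The stated 80% therefore reproduces with no cluster allowance, as the Table 1 row says. Also 372/0.65 = 572.3, which matches the 572 for the Survey phase.

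**2. Inputs the article does not give.** The number of villages, the between-village variance, the ICC and the average number recruited per village are all assumptions below.

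**3. RCT simulation.** N = 372, 33 villages (assumed), allocation balanced within village, gamma village frailty, 2,000 runs. The sandwich is taken at resident level. The Monte Carlo error of a 5% rate is √(0.05 × 0.95/2000) ≈ 0.5 points.

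| Frailty variance | Sandwich SE / true SE (null) | Type I error, no village term | Type I error, stratified Cox |
|---|---|---|---|
| 0.05 | 0.1471/0.1478 = 1.00 | 5.2% | 5.7% |
| 0.10 | 0.1479/0.1438 = 1.03 | 4.4% | 4.6% |
| 0.25 | 0.1506/0.1428 = 1.05 | 3.8% | 4.7% |
| 0.50 | 0.1549/0.1408 = 1.10 | 3.1% | 5.1% |

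With no village variation, type I error without a village term is 5.1%. At a true hazard ratio of 0.80, the unstratified estimate runs from 0.805 to 0.82 over the table's range and the stratified one stays near 0.80. Rejection rates at 0.80, unstratified against stratified, are 29.5% and 29.8% at variance 0.05, 26.8% and 27.0% at 0.10, 25.6% and 28.9% at 0.25, and 19.2% and 25.9% at 0.50. These levels are far below 80% because a hazard ratio of 0.80 is a harder target than risks of 70% against 56%. That is a separate matter; only the contrast within each pair bears on this point. If the sandwich is instead clustered on village, type I error is 5.9% to 6.7%.

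**4. Cost of stratifying when villages do not differ.** A second simulation (30 villages, 70% one-year control risk, hazard ratio 0.68) gives power of 82.9% unstratified and 80.9% stratified with no village variation. That is a loss of about 2 points. At a village SD of 0.3 on the log hazard the two are level (76.2% and 75.8%). At SD 0.5 stratifying gains (73.1% and 76.6%).

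**5. Survey/Cohort, design effect.** For a village-level factor, DE = 1 + (m − 1) × ICC.
- m = 10, ICC = 0.01: 1 + 9 × 0.01 = 1.09, √1.09 = 1.04, so the SE is understated by 1 − 1/1.04 ≈ 4%.
- m = 30, ICC = 0.05: 1 + 29 × 0.05 = 2.45, √2.45 = 1.57, so the SE is understated by 1 − 1/1.57 ≈ 36%.
- A nominal 5% test then has true level 2 × [1 − Φ(1.96/√DE)], which is about 6% and 21% at the two ends.

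**6. Survey/Cohort, simulation.** N = 572, 2.5 years, 33 villages, null village-level factor, Cox model, 1,000 runs.

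| Frailty variance | True SE / SE ignoring village | Type I error, ignoring village | Type I error, village-clustered |
|---|---|---|---|
| 0 | 0.0919/0.0937 = 0.98 | 5.1% | 6.4% |
| 0.05 | 0.1208/0.0943 = 1.28 | 12.0% | 7.0% |
| 0.10 | 0.1477/0.0952 = 1.55 | 21.1% | 6.9% |
| 0.25 | 0.1972/0.0972 = 2.03 | 32.5% | 6.8% |

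With 572/33 ≈ 17.3 residents per village, the squared ratios 1.64, 2.41 and 4.12 correspond to ICCs of 0.64/16.3 ≈ 0.04, 1.41/16.3 ≈ 0.09 and 3.12/16.3 ≈ 0.19. The last two rows therefore lie beyond the ICC range of step 5.

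**The case against.** The strongest reply is that this rests on silence. A journal article gives one sentence per analysis, and a strata statement, the cluster unit of a sandwich or a variance option may sit in a fuller plan. The sandwich may be meant to cluster on village. That stands to this extent: the article shows that use of village is unstated, not that village is unused. It does not dispose of the point. The article chose to name a variance estimator for the RCT and none for the Survey/Cohort models, and Table 1 makes a positive statement about clustering.

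Three stronger readings are tempting, and the documents do not support them.
- A reader might infer that the RCT's standard error is too small and its test invalid. With a resident-level sandwich and allocation within village, the test is at or below nominal. The shift of the hazard ratio towards 1 reflects a marginal rather than a within-village hazard ratio, not a faulty estimate.
- A reader might infer that Table 1 was wrong to drop the cluster adjustment. That row concerns RCT power, and for individual randomisation within village the decision is defensible.
- A reader might infer that all Survey/Cohort intervals are too narrow. The design effect above applies to factors fixed at village level. It does not carry over to factors that vary among residents within a village, where the size is not established here. Village characteristics are also covariates, so village is not ignored altogether.

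**Conclusion.** The point holds as a specification gap with unequal consequences.

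- **RCT:** small and conservative. The standard error is unchanged to about 10% too large and type I error runs from about 5% down to 3%, over assumed frailty variances of 0 to 0.50 with a resident-level sandwich. The effect disappears when villages hardly differ.
- **Survey/Cohort, village-level factors:** the larger concern. If the models are run as written, standard errors are too small by a factor of about 1.04 to 1.57 (design effect about 1.1 to 2.5) for an assumed ICC of 0.01 to 0.05 and 10 to 30 residents per village. The direction holds whenever villages differ; the size depends on those assumptions.

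The change is worth making, mainly for the Survey/Cohort analyses.

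**What to change.** - **RCT:** fit the Cox model with baseline hazard stratified by village, or with a village random effect if many villages have few randomised residents. State the cluster unit of the sandwich variance.
- **Survey/Cohort:** use village-clustered variance or a village random effect, at least for village-level factors. Clustering on village also covers co-residents, since units lie within villages. In the simulation, village clustering still left type I error at 6.4% to 7.0%, so intervals for village-level factors deserve some caution.
- **Table 1, RCT Power calculations row:** keep the decision not to inflate the sample size, but refer to stratified randomisation with a village-stratified analysis instead of stratified sampling. Say that the statement does not extend to the Survey/Cohort analyses.

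The cost is a model statement per analysis and a few words of text. In the stratified RCT model, villages with residents in only one arm contribute no information, and about 2 points of power are lost if villages do not differ. Wider intervals for village-level factors in the Survey/Cohort phases are the intended result.
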